# Increasing engagement with, and effectiveness of, an online CBT-based stress management intervention for employees through the use of an online facilitated bulletin board: study protocol for a pilot randomised controlled trial

**DOI:** 10.1186/s13063-016-1733-2

**Published:** 2016-12-15

**Keywords:** Online, Internet, CBT, Stress, Work

## Abstract

**Background:**

The evidence for the benefits of online cognitive behaviour therapy (CBT)-based programmes delivered in a clinical context is clear, but this evidence does not translate to online CBT-based stress management programmes delivered within a workplace context. One of the challenges to the delivery of online interventions is programme engagement; this challenge is even more acute for interventions delivered in real-world settings such as the workplace. The purpose of this pilot study is to explore the effect of an online facilitated discussion group on engagement, and to estimate the potential effectiveness of an online CBT-based stress management programme.

**Methods:**

This study is a three-arm randomised controlled trial (RCT) comparing a minimally guided, online, CBT-based stress management intervention delivered with and without an online facilitated bulletin board, and a wait list control group. Up to 90 employees from six UK-based organisations will be recruited to the study. Inclusion criteria will include age 18 years or over, elevated levels of stress (as measured on the PSS-10 scale), access to a computer or a tablet and the Internet. The primary outcome measure will be engagement, as defined by the number of logins to the site; secondary outcome measures will include further measures of engagement (the number of pages visited, the number of modules completed and self-report engagement) and measures of effectiveness (psychological distress and subjective wellbeing). Possible moderators will include measures of intervention quality (satisfaction, acceptability, credibility, system usability), time pressure, goal conflict, levels of distress at baseline and job autonomy. Measures will be taken at baseline, 2 weeks (credibility and expectancy measures only), 8 weeks (completion of intervention) and 16 weeks (follow-up). Primary analysis will be conducted on intention-to-treat principles.

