Evidence suggests that increasing guidance from a therapist can lead to greater adherence to online interventions, and result in improved outcomes [8, 12, 16, 23–26]. A facilitated discussion group delivered in the form of a bulletin board could provide a cost-effective and time-efficient means for increasing guidance from a therapist. Although more evidence is needed to support this hypothesis, there is some evidence of improved adherence to bulletin board support: Titov et al. [27], compared guided and nonguided Internet-based CBT for social phobia. The guided condition had access to a facilitated bulletin board and email contact from a therapist. The unguided condition had access to a nonfacilitated bulletin board. The study found that adherence rates for the supported condition were higher than for the unsupported condition (77% and 33% respectively). What was unclear from the study was the extent to which it was the facilitated bulletin board or the email support that successfully provided the additional therapist guidance.

A number of other studies [28–30] have also included discussion groups delivered in the form of bulletin boards as part of an online intervention but have failed to include the groups as a unique research variable so have been unable to identify the impact of the group on the effectiveness of the intervention.

In this study we will examine the effect of an online facilitated bulletin board on engagement with an online CBT-based stress management programme (WorkGuru) and explore whether effectiveness is mediated by engagement. We hypothesise that the bulletin board group will have better engagement outcomes than the minimal support group (MSG), and that these outcomes will result in decreased levels of psychological distress and increased levels of subjective wellbeing at work. Furthermore, we expect to identify moderating factors that influence levels of engagement and effectiveness that are either linked to the quality of the intervention (satisfaction, acceptability, credibility, system usability), time pressure, goal conflict, level of distress at baseline, or job autonomy.

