## Methods

### Study design

A three-arm randomised controlled trial (RCT) will be conducted to compare engagement and effectiveness of a minimally guided, online, CBT-based stress management intervention (WorkGuru) delivered with and without an online facilitated bulletin board. Both active conditions will be compared with a wait list control group (WLC). All participants will have unrestricted access to Care as Usual (CAU), such as counselling and medication, which will be monitored to control for potential confounding effects. The trial will be conducted and reported in line with Consolidated Standards of Reporting Trials (CONSORT) 2010 guidelines [31]. A completed Standard Protocol Items: Recommendations for Interventional Trials (SPIRIT) 2013 Checklist (Additional file 1) and chart (see Table 1) have been completed and submitted for publication. Online assessments will be conducted before randomisation, at 2 weeks (credibility/expectancy measure only), on completion of treatment (8 weeks) and at 16-week follow-up (see Fig. 1).

**Table 1 Tab1:** Standard Protocol Items: Recommendations for Interventional Trials (SPIRIT) schedule of enrolment, interventions and assessment

	Study period (weeks)								
Time point	3/16	4/16	5/16	6/16	7/16	8/16	9/16	10/16	11/16
Enrolment									
Recruitment	X	X	X	X					
Eligibility screen	X	X	X	X					
Informed consent	X	X	X	X					
Allocation	X	X	X	X					
Interventions:									
Discussion group	X	X	X	X	X	X			
Minimal support group (MSG)	X	X	X	X	X	X			
Wait list control group (access to MSG)					X	X	X	X	X
Assessments									
T1	X	X	X	X					
Credibility/expectancy	X	X	X	X	X				
T2			X	X	X				
T3					X	X	X		
Study completion									X

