Demographics will include: age, gender, fluency of written and spoken English, country of birth (UK, non-UK), relationship status, work role, number of working hours (low, middle, high), organisation, education level, income bracket and familiarity with online environment. The full list of measures is depicted in Table 3.

**Table 3 Tab3:** Measures

Measure (number of items)	T1	T2	T3
Primary measure: engagement			
Number of logins to the website		(X)	
Secondary measures: engagement			
Number of modules completed		(X)	
Number of pages visited		(X)	
Self-report engagement		(X)	
Secondary measures: effectiveness			
DASS-21 (21)	X	X	X
IWP Multi-affect Indicator (16)	X	X	X
Other measures			
Number of visits to discussion group		X^a^	
Number of contributions to discussion group		X^a^	
Existing psychological condition	X	X	X
Messages sent to and from coach		(X)	
Demographics	X		
Care as Usual (2)	X	X	X
Time Perception Index (5)	X	X	X
Goal conflicts (3)	X	X	X
Acceptability (6)	X	X	X
Credibility/expectancy (6)		2 weeks	
Level of importance (1)	X		
Negative effects of treatment (1)		X	X
Job autonomy (9)	X		
System Usability Scale (10)		(X)	
Client Satisfaction Questionnaire (8)		(X)	
Online Support Group Questionnaire (9)		X^a^	
Experience of stress management training (1)	X		
Sickness absence for stress-related complaint (1)	X	X	X
Contamination question (1)		X	X

T1 = baseline, T2 = 8 weeks (completion of intervention), T3 = 16 weeks (follow-up)

Groups: X = all three groups, (X) = MSG and discussion group, X^a^ = discussion group only

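### Three of the eight possible moderators (satisfaction, system usability, credibility) are measured only after randomisation, so their association with engagement can be misread as moderation

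*Protocol article*

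**What the plan says.** The Methods part of the abstract lists eight candidates. It begins with four: "Possible moderators will include measures of intervention quality (satisfaction, acceptability, credibility, system usability". It then adds job autonomy, goal conflict, time pressure and distress, the last specified as the baseline level. The Background gives the direction of influence: "we expect to identify moderating factors that influence levels of engagement and effectiveness that are either linked to the quality of the intervention". The same Background section uses mediation as a separate idea (effectiveness mediated by engagement), so moderation is not simply a loose word for any association.

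Table 3 fixes when each candidate is measured. Its legend reads "T1 = baseline, T2 = 8 weeks (completion of intervention), T3 = 16 weeks (follow-up", and a bracketed cross means the two active groups only. The rows beginning "Client Satisfaction Questionnaire (8" and "System Usability Scale (10" each carry one bracketed cross, at T2. Credibility/expectancy appears once, at 2 weeks. Study design confirms that only the baseline assessment precedes randomisation.

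Statistical analyses plans mainly descriptive summaries, with t tests, ANOVAs and correlations as exploratory inference and a promise of caution because this is a pilot. It sets no rule on which time point a moderator must come from.

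**The concern.** A moderator is a characteristic that is settled before treatment starts and across which the treatment effect differs. A rating given after randomisation can be produced by the treatment, or by how much the participant used it. Someone who logs in often may come to find the site usable and satisfying, and someone who gives up early may not. The data from such a rating cannot separate quality driving use from use driving the rating.

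The pilot is meant to inform a definitive trial. A wrong causal reading, for example that better perceived usability raises engagement, could be carried into the design of that trial. A later analysis plan could drop the moderator label, but it could not create baseline values that the measurement schedule does not collect.

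**Working it through.** **Step 1: timing of each candidate (Table 3).**

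| Candidate | Measured at | Groups | Pre-randomisation value? |
|---|---|---|---|
| Satisfaction | T2 (8 weeks) | two active arms | no |
| System usability | T2 (8 weeks) | two active arms | no |
| Credibility | 2 weeks | not marked | no |
| Acceptability | T1, T2, T3 | all three | yes |
| Time pressure (time perception) | T1, T2, T3 | all three | yes |
| Goal conflict | T1, T2, T3 | all three | yes |
| Distress at baseline (DASS-21) | T1, T2, T3 | all three | yes |
| Job autonomy | T1 | all three | yes |

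Three of eight have no baseline value and five do. Of those five, only distress is tied to baseline in the moderator text. Acceptability, time perception and goal conflict are also collected later, so a post-randomisation value could be used for them too.

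**Step 2: order against the outcome.** Logins accrue over 8 weeks. Satisfaction and usability are rated when that period ends. Credibility is rated after 2/8 = 25% of it.

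**Step 3: active versus wait list.** Moderation of an effect on distress or wellbeing requires the moderator in both groups being compared. Satisfaction and usability are absent in the wait list arm, so for that contrast the analysis cannot be done.

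**Step 4: illustration of size.** The document states no figure to reproduce. The 30 per arm comes from Recruitment and randomisation. Everything else here is an assumption: negative binomial logins with means 4 and 6 and dispersion 1.5, and a T2 rating caused only by logins, correlated with them at r. True moderation is zero. Each setting used 4,000 runs at two-sided 5%, with an ordinary linear model containing arm, rating and their product.

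| Assumed r | Interaction significant, 30 per arm | Interaction significant, 20 per arm | Mean arm effect on logins given the rating, 30 per arm (true 2.0) |
|---|---|---|---|
| 0.3 | 13% | 9% | 1.84 |
| 0.5 | 22% | 17% | 1.53 |
| 0.7 | 31% | 23% | 1.07 |

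A baseline variable with no effect stayed at about 5% to 6%. Conditioning on the rating removed (2.00 − 1.84)/2.00 = 8%, (2.00 − 1.53)/2.00 = 24% and (2.00 − 1.07)/2.00 = 47% of the arm effect.

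**Step 5: why an interaction appears.** Let the rating be S = aL + e, with the same a in both arms. The slope of logins L on S within an arm is a·Var(L) / (a²·Var(L) + Var(e)), which rises with Var(L).

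- Var(L) = 4 + 4²/1.5 = 14.67 in one arm and 6 + 6²/1.5 = 30 in the other.
- Pooled variance = (14.67 + 30)/2 + 1² = 23.33.
- For r = 0.5: a = 0.5/√23.33 = 0.1035 and Var(e) = 1 − 0.25 = 0.75.
- Slopes: 0.1035 × 14.67 / (0.0107 × 14.67 + 0.75) = 1.7, and 0.1035 × 30 / (0.0107 × 30 + 0.75) = 2.9.

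The slopes differ by about 1.2 logins per unit of rating although the rating influences nothing. If the two arms had equal login variance, this source of difference would vanish, so the percentages depend on the assumed arm difference. The ambiguity of direction does not depend on it.

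**The case against.** The article is cautious. It calls the moderators possible, plans mainly descriptive statistics, labels the inference exploratory and specifies no moderation model, which an analysis plan may well supply. Five of the eight candidates already have T1 values. Two-week credibility precedes most of the programme, and the T2 ratings precede the T3 distress and wellbeing scores. Moderators are not among the objectives in Aim of the study.

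Much of this stands, and it limits the point. It does not remove it. The promised caution is tied to pilot status and says nothing about temporal order, and a larger sample does not cure reverse causation. Coming before part of an outcome does not make a rating independent of arm or early use.

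A reader might infer more than the document supports:

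- *That reverse causation will be reported as moderation.* The text supports only that it can be misread that way.
- *That the randomised comparison of logins is compromised.* Nothing in Statistical analyses conditions that comparison on these ratings.
- *That a very high chance of a significant satisfaction-login correlation measures the error.* It would be power to detect an association assumed to be real, and a correlation is not a test of moderation.
- *That Care as Usual will be over-adjusted.* Study design says only "which will be monitored to control for potential confounding effects". Table 3 includes a T1 value, and no text says later values will be adjusted for.
- *That many moderator-by-outcome tests will yield false positives.* Multiplicity is a separate matter, and the article does not say every pair will be tested.
- *That the ratings will be missing mainly for non-users.* This is plausible, but the article does not state it.

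**Conclusion.** The point holds for three of the eight candidates. Satisfaction, system usability and credibility are given a role that the measurement schedule cannot support. It is firmest for satisfaction and usability, which are taken after the logins they should explain and are not collected in the wait list arm. It is weaker for credibility, which precedes most of the programme but follows randomisation and the start of exposure.

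The timing conclusion rests on Table 3 alone. The illustrative error rates of 13% to 31% (9% to 23% with 20 per arm) rest on the assumed login distributions and correlations and should be read as showing direction, not as predictions. The primary intention-to-treat result stands as planned. The correction should be made because the pilot's exploratory findings may feed the definitive trial.

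**What to change.** Limit moderator analyses to T1 values: baseline DASS-21, time perception, goal conflict, job autonomy and T1 acceptability. Test each as an arm-by-T1-value interaction and report the results as hypothesis-generating.

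Report satisfaction, usability and post-baseline acceptability descriptively by arm, as process outcomes.

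Treat 2-week credibility as a post-randomisation correlate. If login dates are available, which the article does not say, relate it only to logins after week 2 and note that it may still be affected by arm.

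The change is one of wording in the abstract, the Background and the analysis section, with no new instrument or participants. The price is fewer exploratory claims about intervention quality.

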**Discussion:**

To our knowledge this is the first study to explore the effect of an online discussion group on the engagement and effectiveness of an online CBT-based stress management intervention. This study could provide a solution to the growing problem of poor employee psychological health and begin to address the challenge of increasing engagement with Internet-delivered health interventions.

**Trial registration:**

ClinicalTrials.gov Identifier: NCT02729987. Registered on 18 Mar 2016.

**Electronic supplementary material:**

The online version of this article (doi:10.1186/s13063-016-1733-2) contains supplementary material, which is available to authorized users.

## Background

One in six adults in England meet the diagnostic criteria for at least one common mental health disorder (CMHD), but only 24% of them are receiving any form of treatment [1]. Psychological ill health is the leading cause of sickness absence in the UK accounting for 70 million sick days in 2013 and costing the economy £70–£100 billion per year [2]. Reducing the prevalence of CMHDs is a major public health challenge [1]. One approach to addressing this challenge is to utilise the Internet as a means of delivering evidence-based psychological treatments.

In 2013, 73% of adults in Great Britain used the Internet every day, with 43% using it to seek health information [3]. The Internet has become a natural means for delivering health care information [4], treatment, and prevention programmes [5]. In the UK, computerised cognitive behaviour therapy (CBT) (cCBT) is endorsed by the National Institute for Health and Care Excellence [6] for the treatment of persistent subthreshold depressive symptoms or mild to moderate depression. NICE have also identified cCBT as a promising low-intensity intervention for generalised anxiety disorder [7].

A large number of meta-analyses have found evidence for the delivery of online CBT-based programmes delivered in clinical or community settings for individuals with depression and anxiety [8–12], but the evidence for online psychological interventions delivered in workplace settings is less convincing [13–15].

Researchers have argued that adherence (completing the intervention to the extent that the developers intended it to be used; [16]), engagement (the extent, both in terms of time and frequency, that participants visit the website) and attrition (participants in a study who do not fulfill the research protocol; [16]) all pose challenges to the evaluation and delivery of Internet interventions [17–19]. For Internet interventions delivered in real-world settings (as opposed to clinical research settings), these challenges can be even more acute [20, 21] with as few as 1% of registered users completing all sessions of a freely available online CBT programme for people with panic disorder and agoraphobia [22].

Evidence suggests that increasing guidance from a therapist can lead to greater adherence to online interventions, and result in improved outcomes [8, 12, 16, 23–26]. A facilitated discussion group delivered in the form of a bulletin board could provide a cost-effective and time-efficient means for increasing guidance from a therapist. Although more evidence is needed to support this hypothesis, there is some evidence of improved adherence to bulletin board support: Titov et al. [27], compared guided and nonguided Internet-based CBT for social phobia. The guided condition had access to a facilitated bulletin board and email contact from a therapist. The unguided condition had access to a nonfacilitated bulletin board. The study found that adherence rates for the supported condition were higher than for the unsupported condition (77% and 33% respectively). What was unclear from the study was the extent to which it was the facilitated bulletin board or the email support that successfully provided the additional therapist guidance.

A number of other studies [28–30] have also included discussion groups delivered in the form of bulletin boards as part of an online intervention but have failed to include the groups as a unique research variable so have been unable to identify the impact of the group on the effectiveness of the intervention.

In this study we will examine the effect of an online facilitated bulletin board on engagement with an online CBT-based stress management programme (WorkGuru) and explore whether effectiveness is mediated by engagement. We hypothesise that the bulletin board group will have better engagement outcomes than the minimal support group (MSG), and that these outcomes will result in decreased levels of psychological distress and increased levels of subjective wellbeing at work. Furthermore, we expect to identify moderating factors that influence levels of engagement and effectiveness that are either linked to the quality of the intervention (satisfaction, acceptability, credibility, system usability), time pressure, goal conflict, level of distress at baseline, or job autonomy.

This study is being conducted as a pilot phase of a substantive trial; this will give greater confidence in predicting effect size, refining the optimum engagement of the intervention (adherence) and understanding the accuracy and effectiveness of engagement measures. It will also give a greater understanding of the challenges of conducting this research in a workplace setting.

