### Statistical analyses

Analysis of the primary outcome measure (number of logins to the site) will be conducted on an intention-to-treat basis (participants’ data is analysed in the group that they are randomised to, regardless of treatment they receive or the extent to which they engage with the intervention). Analysis of the secondary measures (psychological distress and subjective wellbeing) will also be conducted on an intention-to-treat basis. Missing data will be imputed using the Last Observation Carried Forward method. For the engagement measures where no previous data is available, missing data will be imputed using the group mean. To check the robustness of the primary findings, sensitivity analysis including a per-protocol analysis will be performed. Per-protocol is defined as three or more logins to the WorkGuru site. This baseline has been identified from average login data from the site and reflects login data from other studies (for a summary of login data for online health promotion interventions see [23]).

Primary and secondary hypotheses will be explored using predominantly descriptive statistics. The means and/or medians (as appropriate) will be reported with standard deviations. Ninety-five percent confidence intervals will be calculated. Standardised effect sizes will be calculated using Cohen’s *d* and, where appropriate, odds ratios will be reported. Exploratory inferential analysis will be performed using *t* tests, analyses of variance (ANOVAs) and correlations as appropriate. In recognition that this is a pilot study caution will be taken in interpreting and reporting these results.

Baseline differences between groups will be explored using the chi-square test and ANOVA (as appropriate) and, where possible, we will compare demographics of trial participants with the workforce of each organisation to see if trial participants are representative of the workforce.

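### Carrying the last observation forward for DASS-21 and IWP can produce a spurious link between logins and improvement in a pilot that means to relate engagement to outcome

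*Protocol article*

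**What the plan says.** The Background of the protocol article sets the question: the study will "explore whether effectiveness is mediated by engagement". It adds a directional hypothesis, that the board group will engage better and that "these outcomes will result in decreased levels of psychological distress and increased levels of subjective wellbeing at work". The Discussion returns to this when it says the pilot should improve understanding of utilisation measures and their relation to outcome.

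The Statistical analyses section says: "Primary and secondary hypotheses will be explored using predominantly descriptive statistics". It adds exploratory t tests, "analyses of variance (ANOVAs) and correlations as appropriate", and promises caution because this is a pilot.

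For missing values it fixes two rules. The general rule is "Missing data will be imputed using the Last Observation Carried Forward method". The second reads: "For the engagement measures where no previous data is available, missing data will be imputed using the group mean". The only sensitivity analysis it names is per protocol: "Per-protocol is defined as three or more logins to the WorkGuru site".

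Table 3 collects logins, pages and modules in the two active arms only, and DASS-21 and IWP in all three arms at baseline, 8 weeks and 16 weeks.

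**The concern.** Under last observation carried forward (LOCF), a participant with neither follow-up score keeps the baseline score, so the change is exactly zero. Someone seen at 8 weeks but not at 16 keeps the 8-week score. Site-recorded use, by contrast, can be known for everyone in the active arms. If people who use the site little also tend to miss the questionnaires, the imputation attaches zero change mainly to low login counts. If those who do return improve on average, by natural recovery or regression to the mean, the data then show more improvement at higher logins even though the programme did nothing.

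This error favours the study's own hypothesis. A spurious login-outcome gradient would colour what the pilot passes on to the definitive trial about how use relates to benefit.

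**Working it through.** **Plan's own figures.** The article states no attrition rate, login distribution, expected change or power for this question, so there is nothing to reproduce. Two inputs can be read from it. With 30 per arm, the arms with login data hold 2 × 30 = 60 participants. Entry requires PSS-10 of at least 20, and 13.02 + 6.35 = 19.37, so participants enter about one SD above the cited population mean. All other inputs below are assumptions.

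**Mechanism.** Let δ be the average improvement unrelated to the programme, and p(L) the probability of no follow-up at login count L. Let improvement be independent of logins, and of dropout given logins. Then under LOCF

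E[recorded improvement | L] = δ × (1 − p(L)).

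This varies with L only if δ ≠ 0 and p(L) is not constant. Splitting at three logins, the expected spurious gap is δ × (p_low − p_high).

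**First simulation.** Inputs: 3,000 runs per scenario, n = 60, no programme effect, overdispersed logins with mean 4 (about 47% below three), baseline/follow-up correlation 0.6. Tests at 5%: correlation of log(1 + logins) with change, and a t test of three or more logins against fewer.

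| Improvement δ (SD) | Dropout low/high users | Expected gap (SD) | Correlation, LOCF | t test, LOCF |
|---|---|---|---|---|
| 0 | all three patterns | 0 | 4.1-4.6% | 4.0-4.7% |
| 0.3-0.8 | 30/30% | 0 | 4.8-5.1% | 4.7-5.3% |
| 0.3 | 50/20% | 0.3 × 0.30 = 0.09 | 7.2% | 8.2% |
| 0.5 | 50/20% | 0.5 × 0.30 = 0.15 | 9.5% | 13.1% |
| 0.8 | 50/20% | 0.8 × 0.30 = 0.24 | 15.1% | 21.4% |
| 0.3 | 70/15% | 0.3 × 0.55 = 0.165 | 11.9% | 16.7% |
| 0.5 | 70/15% | 0.5 × 0.55 = 0.275 | 22.6% | 33.0% |
| 0.8 | 70/15% | 0.8 × 0.55 = 0.44 | 43.6% | 60.5% |

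In the last six rows the mean spurious correlation is 0.05 to 0.23 in the favourable direction. On observed data only, all 12 scenarios give 4.4-5.8% (correlation) and 4.1-5.8% (t test). Complete cases are valid here because the simulated dropout depends only on logins.

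**Same data, mediation regression.** Regress outcome on logins, arm and baseline, with the board assumed to double logins. In the same six conditions, LOCF gives 6.1-43.5% false positives on the login-outcome path and a spurious indirect effect of 0.02 to 0.105 SD in favour of engagement. Without LOCF the path rejects in 4.5-6.1% of runs and the mean indirect effect is within 0.003 SD of zero. So the cause is the imputation, not the test.

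**Second simulation, other login assumptions.** Inputs: n = 60, negative binomial logins (dispersion 1), mean 5 in returners, improvement 0.3 or 0.5 (SD of change 0.8) independent of logins, dropouts set to zero change, Pearson correlation with raw logins.

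| Mean logins, returners vs dropouts | 20% dropout | 40% | 60% |
|---|---|---|---|
| 5 vs 1.5 | 9-10% | 16-22% | 24-35% |
| 5 vs 3.5 | about 6% | 7-10% | 11-13% |
| 5 vs 5 | 5-6% | 5-6% | 5-6% |
| 5 vs 1.5, zero average improvement | 6.7% | 10.6% | 16.9% |

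Repeat runs move these by one or two percentage points. In the first row the mean correlation is 0.05-0.08, 0.09-0.14 and about 0.12-0.19, and most rejections are in the favourable direction. Among returners only, the rate is 5-6% and the mean correlation about zero. In the last row the mean correlation is 0.00: the excess comes from unequal variance and does not favour either direction.

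**The case against.** - **The missing mediation model is not an error.** A reader might infer that the plan is wrong because it names only t tests, ANOVAs and correlations. A condensed article may leave the model to a SAP or full protocol. The simple tests are also not the source of the bias. This stands, and the point is confined to LOCF.
- **The association is not automatic.** A reader might infer that LOCF ties low use to no change by construction. It does so only with both average change and login-related dropout, and the article quantifies neither. Questionnaires run on Qualtrics, separate from the WorkGuru site, so not logging in does not mechanically mean missing an assessment. Screening is on PSS-10 while the outcomes are DASS-21 and IWP, so regression to the mean may be weaker on the outcomes. All this stands. Both conditions remain plausible: entry is on a raised stress score, and the Background names engagement and attrition as acute problems in real-world settings.
- **The sizes are assumed.** They are. With a mild login contrast the inflation is small, and part of the excess under a strong contrast is not directional.
- **The pilot is cautious.** Inference is exploratory, the Discussion calls the study underpowered, and mediation is not a listed objective. The objective on adherence thresholds rests on how far participants engage, not on a login-outcome correlation. So a reader who infers that the pilot would announce that engagement drives benefit goes beyond the text. This lowers the severity, but caution in wording does not remove a directional bias from an estimate.
- **Other sensitivity analyses may follow.** The wording leaves room for more than the per-protocol analysis. The one named selects on logins and does not replace carried-forward values.

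**Conclusion.** The point holds in a conditional form. LOCF is a stated choice for the outcomes that the article wants to relate to engagement, and it can produce a favourable login-improvement association when the programme has no effect. With 60 active participants, 20-60% dropout and 0.3-0.5 SD of unrelated improvement, the correlation's false-positive rate is about 9-35% for a strong login contrast (5 versus 1.5) and 6-13% for a mild one (5 versus 3.5), against about 5% without LOCF. Dropout, login and improvement values are assumptions. If either condition is absent, there is no directional bias. The weight is modest, given the exploratory pilot status, but the change is cheap and worth making.

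**What to change.** In Statistical analyses, replace LOCF for DASS-21 and IWP, at least in every analysis relating engagement to outcome. Use a mixed model or multiple imputation that includes baseline score, arm and logins. The wait list arm has no logins, so the login term applies within the two active arms. Keep LOCF, if at all, as a sensitivity analysis. Report login-outcome results as associations: engagement is not randomised, and confounding remains even with sound handling of missing data.

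Cost: a few sentences, a little more analysis work on data already planned, and wider intervals. The replacement assumes that data are missing at random given the included variables, which should be stated.
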